## Abstract

**Background:**

Zimbabwe currently faces a rapidly escalating burden of noncommunicable diseases (NCDs) concurrently with persistent communicable disease challenges, resulting in profound epidemiological differences between rural and urban populations. To effectively address this evolving epidemiological landscape and guide evidence-based public health interventions, reliable and high-quality longitudinal data are essential for capturing temporal shifts and contextual determinants often overlooked by conventional health information systems.

**Objective:**

This protocol details the methodology for establishing a health and demographic surveillance system (HDSS), a longitudinal, population-based cohort designed to continuously monitor the prevalence, incidence, and key determinants of NCDs, specifically cardiovascular diseases and diabetes, and their associated risk factors in selected rural (Mt Darwin) and urban (Bindura) sites in Mashonaland Central Province over a 5-year period (2024‐2029).

**Methods:**

The HDSS uses a stratified multistage sampling design to recruit adults (aged ≥18 y) residing across 2 rural and 2 urban wards. Initial activities include comprehensive community profiling and household mapping, followed by a rigorous baseline survey, with systematic follow-ups scheduled every year. Data encompass essential domains such as vital events, migration patterns, detailed social determinants of health, health behaviors, self-reported and clinically assessed NCDs, physical examinations (including height, weight, blood pressure, and waist/hip circumference), biochemical markers (fasting glucose, lipid profiles, and urine sodium/creatinine), and standardized verbal autopsies. Data capture will make use of REDCap (Research Electronic Data Capture) to facilitate real-time data entry and validation. The protocol is underpinned by rigorous quality assurance procedures, continuous community engagement, and comprehensive ethical oversight.

**Results:**

The Zimbabwe HDSS received ethical approval on July 30, 2024 (MRCZ/A/3191). Baseline data collection was completed in Mt Darwin (rural site) in December 2024 and in Bindura (urban site) in March 2025. Statistical analysis of baseline NCD prevalence, risk factor distributions, and rural-urban comparisons is underway, with findings expected to be submitted for publication by the end of 2026. The first annual longitudinal follow-up round is planned for the second quarter of 2027, subject to funding availability, with subsequent rounds scheduled annually through 2029. Longitudinal incidence estimates and NCD trend analyses are expected to be published progressively from 2026 to 2029.

**Conclusions:**

This community HDSS addresses a critical evidence deficit within Zimbabwe’s national health information infrastructure. By implementing an ethical, sustainable, and community-engaged research methodology, the HDSS serves as a potent regional model. It is designed to generate actionable, policy-relevant data for national health authorities and stakeholders, thereby accelerating the country’s NCD prevention and control agenda while simultaneously acting as an enduring platform for academic innovation, capacity building, and policy translation efforts targeting both rural and urban health disparities.

## Introduction

### Burden of Noncommunicable Diseases

Noncommunicable diseases (NCDs)—cardiovascular diseases, diabetes, cancer, and chronic respiratory diseases—account for 71% of global deaths annually, with low- and middle-income countries bearing a disproportionate 80% of NCD mortality [1,2]. Sub-Saharan Africa faces a particularly complex dual burden: persistently high communicable disease rates coexist with rapidly rising NCD prevalence, creating unprecedented challenges for health systems designed primarily for acute infectious diseases [3]. Zimbabwe exemplifies this epidemiological transition, with NCDs now accounting for 32% of all deaths in 2023, hypertension prevalence ranging from 18% to 38% across different populations, and diabetes increasing dramatically from 0.44% in the pre-1980 period to 5.7% in recent years [4,5]. Critically, many cases remain undiagnosed and untreated, with individuals accessing care only when serious complications arise [6].

Rural-urban disparities add substantial complexity to this landscape. Urban residents face heightened exposure to NCD risk factors, including energy-dense diets, physical inactivity, tobacco use, and alcohol consumption [7], while rural populations encounter limited health infrastructure, severe personnel shortages, inadequate diagnostic capacity, and substantial treatment delays [8]. Migration and urbanization fundamentally alter disease risk profiles as individuals transition between environments [9]. This geographic divide is further complicated by the NCD-HIV intersection, where poor chronic disease control has emerged as the strongest predictor of mortality in the antiretroviral therapy era [10].

### Gaps in Existing Health Information Systems

Current surveillance systems suffer critical inadequacies that impede effective NCD response. Weak Civil Registration and Vital Statistics systems create fundamental gaps in understanding mortality dynamics, with many deaths occurring outside facilities and never recorded [11,12]. Facility-based surveillance captures only individuals accessing formal health care, systematically missing those who are undiagnosed, use traditional providers, or face access barriers [13]. This dramatically underestimates burden for NCDs with substantial asymptomatic populations [14]. Cross-sectional surveys cannot track longitudinal trends, assess incidence, or establish temporal relationships [15]. Self-reported data substantially underestimate NCD prevalence compared to biomarker measurement [14]. Systems lack the geographic granularity needed for targeted interventions [16].

### Limitations of Demographic and Health Surveys

Zimbabwe has a well-established tradition of population-based health surveys, anchored by the Demographic and Health Survey (DHS) program, which has been conducted 7 times since 1988. DHSs, while valuable, have significant constraints for NCD surveillance. Episodic conduct at typically 5-year intervals creates temporal gaps during which critical changes occur undetected [16]. The cross-sectional design precludes tracking individuals, assessing incidence, or establishing causal relationships [17], particularly problematic for NCDs developing over decades [10]. DHS has historically focused on maternal-child health, with limited adult NCD coverage [18]. Rapid sociocultural changes necessitate continuous surveillance to capture evolving risk profiles [19].

### Health and Demographic Surveillance Systems: A Solution

Health and demographic surveillance systems (HDSSs) provide continuous, longitudinal, population-based measurement of demographic, health, and social indicators within geographically defined populations [20,21]. HDSSs conduct regular household visits at intervals of 4 to 12 months, systematically updating births, deaths, migrations, and health events for all residents, enabling accurate calculation of rates and individual-level tracking over time [22]. This longitudinal design allows incidence assessment, prospective risk factor identification, intervention evaluation, and temporal trend monitoring that are impossible with cross-sectional surveys [15].

HDSSs differ fundamentally from other surveillance approaches in ways directly relevant to NCD monitoring. Unlike facility-based surveillance that captures only health care–seeking individuals, HDSSs conduct active community-based surveillance reaching all residents regardless of care-seeking behavior, health status, or socioeconomic position [11]. Unlike sentinel systems that monitor selected populations or facilities, HDSSs provide comprehensive data for entire defined populations, enabling unbiased prevalence and incidence estimation [23]. Unlike DHS, which provides periodic snapshots, HDSSs generate continuous real-time data enabling detection of emerging trends and rapid public health response [24].

Concrete examples demonstrate HDSS value for NCD surveillance. Verbal autopsies conducted in 6 eastern and southern African HDSSs revealed stable NCD mortality rates from 1995 to 2019 despite substantial declines in communicable disease mortality—epidemiological patterns that would be invisible to episodic cross-sectional surveys [25]. In rural South Africa, HDSS data showed that life-years lost to NCDs exceeded pre-HIV epidemic levels by 2014‐2018, demonstrating the system’s capacity to detect critical epidemiological transitions and inform policy priorities [19].

HDSSs employ standardized instruments ensuring data comparability across sites and over time [21], maintain population-based sampling frames covering all residents [20], and integrate multiple data sources, including household surveys, health facility records, and vital events registration [26]. They serve as platforms for nested studies, randomized trials, and intervention evaluations [27], generating evidence directly applicable to policy and practice.

### Rationale for Rural-Urban HDSS in Zimbabwe

Establishing an HDSS spanning rural and urban Zimbabwe strategically addresses identified surveillance gaps through direct rural-urban comparison. The rationale is 3-fold. First, NCD burden, determinants, and health consequences differ substantially between rural and urban settings, requiring context-specific evidence [17]. Second, Zimbabwe’s rapid urbanization, with increasing rural-to-urban migration, fundamentally alters population health profiles, necessitating surveillance systems that capture these dynamic transitions [28]. Third, health system capacity, infrastructure, service delivery models, and resource availability differ markedly between rural and urban areas [29], requiring geographically tailored intervention strategies.

### Study Aims

This paper describes the establishment of a Zimbabwe HDSS to address critical NCD surveillance gaps through 4 specific aims:

Establish a longitudinal, population-based HDSS spanning rural and urban sites to generate accurate, timely data on demographic dynamics, NCD burden, risk factors, and health care access through continuous household surveillance with regular follow-up.Characterize prevalence, incidence, and temporal trends of major NCDs—hypertension, diabetes, cardiovascular diseases, and chronic respiratory diseases—with particular emphasis on identifying undiagnosed and untreated cases through active case-finding and objective biomarker measurement.Quantify rural-urban differences in NCD burden, risk factor exposure profiles, health care–seeking behavior, treatment access, and health outcomes to inform geographically targeted interventions and evidence-based resource allocation.Generate actionable evidence informing national NCD policy development, strategic planning, resource allocation decisions, and intervention design through systematic integration with existing health systems and continuous stakeholder engagement.

By addressing fundamental gaps in existing surveillance infrastructure, this HDSS will provide the continuous, geographically granular, longitudinal data essential for evidence-based NCD prevention and control in Zimbabwe’s rapidly evolving epidemiological landscape.

## Methods

### Study Design

This protocol outlines the methodology for a prospective, longitudinal HDSS established in geographically defined rural and urban communities in Zimbabwe. The HDSS is designed to collect, monitor, and compare comprehensive health, demographic, and behavioral data critical to NCDs over a continuous 5-year period (2024‐2029). This systematic approach aligns with established HDSS methodologies that enable dynamic, population-based measurement and repeated assessments, which are vital for characterizing the evolution of NCD burdens across distinct social and economic contexts. A schematic flowchart providing an overview of the HDSS workflow across all 4 phases has been developed (Figure 1).

**Figure 1. F1:**
[figure not shown]
Health and demographic surveillance system workflow in Mashonaland Central Province, Zimbabwe, 2025. BP: blood pressure; GIS: geographic information system; HDSS: health and demographic surveillance system; NCD: noncommunicable disease; POC: point-of-care; REDCap: Research Electronic Data Capture; WHO STEPS: World Health Organization STEPwise approach to NCD risk factor surveillance.

### Study Setting

The HDSS implementation will occur across 2 purposively selected districts within Mashonaland Central Province, Zimbabwe: Mt Darwin (rural site) and Bindura (urban site). Mt Darwin District encompasses approximately 1500 km^2^, hosting an estimated population of around 120,000 residents. The population predominantly relies on subsistence and small-scale commercial farming (eg, maize and tobacco), with sociodemographic indicators suggesting moderate educational attainment and agriculture-based household income. Health care services are provided by the Mt Darwin District Hospital and smaller rural clinics. Bindura District represents the urban setting, covering roughly 2800 km^2^ with an estimated population of 140,000 distributed across 14 wards. Bindura exhibits higher population density and a diversified economy, including mining (Bindura Nickel Corporation), trading, and academic communities linked to Bindura University. Health infrastructure is comparatively advanced, featuring the Bindura Provincial Hospital (a 200-bed referral facility) complemented by an extended clinic network. The HDSS will utilize 4 purposively selected wards (2 rural and 2 urban) to capture these socioeconomic and epidemiological contrasts.

### Community Profiling and Household Mapping

The initial phase involves rigorous community profiling, which synthesizes national census data, local administrative knowledge, geographic information systems (GIS), and satellite imagery analysis. This process systematically documents contextual factors, including local history; population characteristics (demographic and socioeconomic indicators); transportation and communication systems; employment and income sources; housing patterns; educational facilities (including information and communication technology use and teacher capacity); health facilities; financial institutions; nongovernmental organizations; recreational centers; agricultural and veterinary services; places of worship; and environmental degradation (eg, deforestation for tobacco curing, artisanal mining, and silted reservoirs). Governmental schemes, including state-administered agricultural support, social cash transfers, food assistance, and public works programs operating in the ward, were assessed. As part of community profiling, the availability of mobile network providers within each ward is documented as a proxy indicator of network coverage and field communication feasibility. It is acknowledged that enumeration of service providers is a limited proxy that does not capture household- or individual-level digital access, affordability, internet literacy, or device ownership; comprehensive digital readiness assessment is beyond the scope of the current protocol but is identified as an important priority for future HDSS rounds.

Household mapping is conducted as a structured, multistep process to generate a complete and reproducible sampling frame for longitudinal surveillance. First, existing Enumeration Areas (EAs) from the most recent national census are obtained from the Zimbabwe National Statistics Agency and imported into a GIS platform (QGIS) to delineate EA boundaries for the selected wards. Second, trained field mappers conduct a door-to-door household listing within each EA using handheld GPS-enabled tablets preloaded with custom forms developed in REDCap (Research Electronic Data Capture), recording the precise geographic coordinates of each dwelling, its EA code, and basic dwelling characteristics (eg, structure type and occupancy status). Third, each residential structure that meets the HDSS definition of a household (people who “eat from the same pot” and usually sleep in the dwelling for at least 3 of the last 6 mo) is assigned a unique household identification (HHID) code, which is physically labeled on the dwelling (eg, paint or sticker) and simultaneously captured electronically. Fourth, the georeferenced household list (HHID, EA code, and GPS coordinates) is exported from the data collection platform and integrated into the central HDSS database, where it is linked to the GIS layer to enable spatial checks, duplicate detection, and verification of coverage. The resulting quality-checked household register constitutes the sampling frame for all baseline and follow-up HDSS rounds.

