### Study Population and Sampling

The study population includes all adults aged 18 years and older who are usual residents in the defined rural and urban HDSS areas (ie, the 4 selected wards) at the time of the baseline census. For operational purposes, a “usual resident” is defined as an individual who has lived in the household for at least 3 of the previous 6 months or who intends to stay for at least 6 months, consistent with HDSS standards. As an HDSS, the system aims for exhaustive inclusion of all eligible adults within the mapped households rather than a sample-based design.

Within each mapped household (HHID), fieldworkers use a standardized roster module on the tablet to list all household members, recording name, sex, age, relationship to head of household, and residency status. Adults (aged ≥18 y) who meet the residency criterion and provide informed consent are included and invited to complete individual-level interviews and measurements. Exclusion criteria are (1) individuals younger than 18 years; (2) visitors or short-term guests who do not meet the residency definition; (3) individuals who are unable to provide informed consent and for whom no appropriate consenting procedure is approved; and (4) individuals who explicitly decline participation. For temporarily absent eligible adults (eg, at work or school), at least 2 repeat visits are scheduled at different times and days before classifying them as nonresponders for that round. This approach ensures near-complete coverage of the adult resident population in both communities.

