### Follow-Up Procedures

Following the baseline census, longitudinal data collection rounds will be implemented annually over the 5-year surveillance period. Using the existing household and individual registers, field teams revisit each HHID and reverify the household roster, updating entries for births, deaths, in-migrations, out-migrations, and changes in marital status. Migration events are classified and dated using standard HDSS definitions, enabling calculation of person-time at risk and net migration rates. Migration events are identified and documented during each annual household roster update. New residents found in a previously mapped household who meet the standard residency criterion (at least 3 of the last 6 mo or intending to stay at least 6 mo) are classified as in-migrants, assigned a unique individual ID, and enrolled prospectively, with their origin and date of arrival recorded. Previously enrolled individuals confirmed by household members to have permanently departed the HDSS ward boundaries are classified as out-migrants, with their date of departure, destination, and reason for migration recorded and their follow-up record closed from that date, contributing person-time up to departure. Individuals who return after out-migration are reenrolled under their original ID, ensuring longitudinal continuity.

At each round, eligible adults are recontacted for updated interviews and measurements to estimate NCD prevalence and incidence, monitor changes in health-related behaviors and attitudes, and track risk factors over time. All recorded deaths are subjected to verbal autopsy using the WHO 2016 [31] standardized instrument administered on tablets; data are processed with automated cause-of-death assignment tools (eg, InterVA or InSilicoVA), given the limitations of vital registration in this setting.

Participant retention is managed through a structured recontact protocol whereby temporarily absent individuals receive at least 2 repeat visits at different times before being recorded as noncontactable for that round. At each round, the baseline characteristics of participants lost to follow-up will be compared with those retained to assess and account for potential attrition bias.

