### Data Analysis

The analytic plan encompasses descriptive statistics, robust prevalence and incidence estimations, and comparative analyses designed to quantify rural versus urban differences. Statistical software, primarily Stata (version 18; StataCorp LLC), will be employed. Numeric variables will be summarized using medians and IQRs, while categorical variables will be summarized using proportions. Logistic regression analyses (univariable and multivariable) will be used to identify and assess risk factors associated with NCDs, employing a hierarchical approach and stepwise backward elimination. The calculation of birth, mortality, prevalence, and incidence rates will be executed accordingly, and chi-square tests for trend will be used to analyze changes in NCD burden over time. Advanced statistical techniques, including regression and survival analyses, will facilitate robust estimation of NCD determinants and epidemiological transitions between the distinct study settings.

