## Results

The Zimbabwe HDSS was granted ethical approval by the Medical Research Council of Zimbabwe on July 30, 2024. Community profiling and household mapping were completed in both sites in the third quarter of 2024. Baseline data collection was completed in Mt Darwin (rural site) in December 2024 and in Bindura (urban site) in March 2025. Data cleaning and quality assurance procedures for the baseline dataset were initiated in April 2025, and statistical analysis of baseline prevalence, risk factor distributions, and rural-urban comparisons is projected for completion by the first quarter of 2026, with findings expected to be submitted for publication by the end of 2026. The first annual longitudinal follow-up round is planned for the second quarter of 2027, subject to funding availability. Subsequent follow-up rounds are scheduled annually through 2029, with longitudinal incidence estimates, demographic event rates, and NCD trend analyses expected to be published progressively from 2026 onward.

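### Follow-up rounds keep the 2024 household register as their frame, so dwellings built later in the four wards are not covered, and the named trend test cannot separate a changing age mix from real change

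*Protocol article*

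**What the plan says.** All references are to the protocol article.

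- **Frame.** Community Profiling and Household Mapping: "The resulting quality-checked household register constitutes the sampling frame for all baseline and follow-up HDSS rounds". Results dates the mapping: "Community profiling and household mapping were completed in both sites in the third quarter of 2024".
- **Field procedure.** Follow-Up Procedures: "Using the existing household and individual registers, field teams revisit each HHID and reverify the household roster". The in-migrant rule there covers "New residents found in a previously mapped household who meet the standard residency criterion". People who left and come back are also covered: "Individuals who return after out-migration are reenrolled under their original ID, ensuring longitudinal continuity".
- **Growth of the frame.** Future Plans speaks of extending to further wards and districts. No section describes adding new dwellings inside the present four wards.
- **Who is measured.** Study Population and Sampling dates the adult population with the words "at the time of the baseline census". Follow-Up Procedures says: "At each round, eligible adults are recontacted for updated interviews and measurements". Neither section says what happens when a listed minor turns 18.
- **Analysis of change.** Data Analysis: "chi-square tests for trend will be used to analyze changes in NCD burden over time". The same section also names multivariable logistic regression and survival analysis, but does not assign them to the between-round trend in prevalence.

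**The concern.** Two separate things are at stake.

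**Coverage.** The rationale for the study is urbanisation and rural-to-urban movement. A frame that takes in no new dwellings loses part of the population whose change the system is meant to record. It also leaves a gap for internal movers: someone who moves to an unlisted dwelling in the same ward has not left the ward, so is not an out-migrant, and the article gives no way of finding that person.

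**Composition.** Hypertension and diabetes become more common with age. If the age mix of those measured shifts between rounds, crude prevalence shifts even when risk at each age is constant. Field teams could read the entry rule at 18 either way, and the two readings give different age structures. A chi-square test for trend on counts by round reports both kinds of change as one.

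**Working it through.** **Coverage: reading the rules together**

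1. The register is the frame for every round, and mapping was completed in the third quarter of 2024.
2. The first follow-up is planned for the second quarter of 2027. From the end of September 2024 to the start of April 2027 is 2.5 years, so the frame is at least that old at first reuse. It is more than four years old in 2029.
3. Teams go to existing household codes. The rule for newcomers requires a previously mapped household.
4. A dwelling built after mapping has no code, is not revisited, and its residents do not meet the newcomer rule.

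The resulting bias in prevalence for a round is u × (P_covered − P_uncovered), where u is the share of current adults living outside the frame. The documents give neither u nor the difference, so this part cannot be sized. That it is larger at the urban site is a judgement from the article's own account of migration, not a stated fact.

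**Composition: how far crude prevalence can move with no real change**

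The article has no figure of its own for such drift, so there is none to reproduce. Inputs from Study Population and Sampling are the 30% baseline hypertension prevalence and the 2-point annual change the study wants to detect. Everything else is assumed: a stable adult age structure, population growth of 1% to 3% a year, Gompertz mortality, and a logistic age slope of 0.03 to 0.06 per year calibrated to 30% overall.

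Crude prevalence is P = Σ w(a) p(a), with w(a) the share at age a. Holding p(a) constant and moving only w(a) gives:

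| Who enters the panel | After 2 years | After 5 years |
|---|---|---|
| Residents turning 18 enrolled, no migration | 30.0% | 30.0% |
| Nobody enters | 30.7% to 31.6% | 31.9% to 34.2% |
| 5% yearly turnover, in-migrants with the same age mix, no entry at 18 | – | 31.6% to 33.6% |
| 5% leave yearly at all ages, replaced by in-migrants aged 18 to 34 | – | 29.0% to 30.7% |

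The last row is the most sensitive to the mortality curve. Other plausible curves raise it by roughly a point, so even its sign is not settled.

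One-step check of the second row. At 3% growth, 18-year-olds make up 0.043 of adults. Removing one year's entrants, with assumed prevalence q at age 18, gives (0.30 − 0.043q)/(1 − 0.043).
- q = 0.20: 0.2914/0.957 = 30.4%
- q = 0.12: 0.29484/0.957 = 30.8%

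That agrees with the closed-panel drift of 0.4 to 0.8 points a year.

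**Against the study's own yardstick.** The 2-point target is annual, so the like-for-like comparison is 0.4/2 to 0.8/2, or 20% to 40% of the target in a closed panel. Over the long first gap, the closed panel has gained 0.7 to 1.6 points by year 2. These are worst-case rows, because they need both no entry at 18 and no young in-migration.

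**The case against.** The strongest reply is that the article does not close the panel. Rosters record everyone in the household with age and are reverified each round. The under-18 exclusion lapses at 18, the sampling text invites every resident adult of a sampled household, and returnees are re-enrolled. A reader might infer that in-migration is the only way in. The documents do not support that: entry at 18 is ambiguous, not barred.

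A reader might also infer that crude prevalence will rise for no real reason. That does not follow either. With entry at 18 and no migration it stays at 30.0%, and young in-migrants, whom the article does enrol, can cancel or reverse a rise. The age gradient and migration rates are not in the documents. Setting several years of accumulated drift against an annual target would also overstate the problem.

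Finally, age standardisation is commonly left to an analysis plan, which is not shown, and the article never says its trend will be crude. That stands: its absence is not in itself an error. What remains is that the one method named for change over time has no age term.

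On coverage the reply is weaker. The article does not say outright that the register is frozen, but both the frame sentence and the newcomer rule point to mapped households, and nothing in the text adds a dwelling.

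**Conclusion.** The coverage point holds on the text. As written, dwellings built after the 2024 mapping in the four wards are not covered in any follow-up round, and the gap widens with time. Its size is unknown.

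The composition point holds in a limited form. The rule at age 18 is unclear, and the named trend test cannot separate age mix from real change. Crude prevalence could rise, stay flat or fall. The assumption-based range is about -1 to +4 points over five years from 30% (29.0% to 34.2%), and it rests on the growth, mortality, age-slope and migration assumptions above. It shows that the entry rule matters; it does not forecast a result.

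The plan should be amended before the first follow-up round.

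**What to change.** 1. **New dwellings.** At each round, add them by a half-open-interval rule: any new dwelling found between a sampled household and the next listed one enters the frame. This needs a fixed listing order. Alternatively, re-list the enumeration areas before each round, which suits areas with much new building.
2. **Age 18.** State in one sentence under Follow-Up Procedures that roster members who reach 18 and meet the residency criterion are invited at the next round.
3. **Trend analysis.** Base between-round trends on prevalence standardised to one fixed age-sex distribution, for example the pooled baseline roster, or on an age-sex-adjusted model. Report within-person change separately as incidence.

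The cost is modest extra listing during visits already planned, a few added interviews per round, and a standardisation step that uses age and sex already on the roster. No follow-up round has taken place, so nothing collected has to be redone.
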